### Trial flow

At baseline, an ECG, a transthoracic echocardiogram, a QoL questionnaire (EQ-5D-5L and AFEQT), as well as certain blood tests will be performed for every patient. Randomization takes place at baseline. Patients who are in the intervention group will receive cryoballoon-guided AF ablation within 21 days from baseline. Patients who are in the control group will receive standard-of-care only, which is defined as a rhythm control strategy with electric cardioversion (if necessary) and AAD. Both arms will receive an ILR for continuous rhythm monitoring. Regular follow-up evaluation is planned for both groups after 3, 6, and 12 months. An extended follow-up evaluation of the ILR events up to 24 and 36 months is planned, including a patient phone call at 24 and 36 months for detection of adverse events, and QoL assessment (sent via letter).

Randomization is based on a 1:1 ratio into 2 study arms, as follows: (i) cryo AF ablation—pulmonary vein isolation (PVI) performed with a cryoballoon ablation system; and (ii) usual care—AAD therapy based on the decision of the investigator according to current European Society of Cardiology (ESC) guidelines,^1^ including electrical cardioversion, if necessary. Both arms will have a blanking period or an AAD optimization period of 3 months, during which adaptation of the therapy will be allows (Fig. 1).

**Figure 1 fig1:**
[figure not shown]
Study flowchart. AF, atrial fibrillation.

### Data collection within the study

Data collection within the study, including baseline testing, is reported in Table 2.

**Table 2 tbl2:** Data collection within the study

Data collection	Baseline	ILR-Implantation	Ablation	Pre-discharge	3-mo	6-mo	12-mo	24-mo	36-mo
(d 0 = presenting in ER with recent-onset AF)	(0–21 d, prior to ILR-implantation)	(0–21 d, prior to ablation / AAT)	(0–21 d) (Ablation group)	(Ablation group)	(+/- 7 da)	(+/- 7 d)	(+/- 7 d)	(+/- 14 d)	(+/- 36 d)
Informed consent	x								
Inclusion / exclusion	x								
Demographic data	x								
Medical history	x								
Medication regime (cardiovascular)	x		x	x	x	x	x		
Randomization	x								
Procedural data (only ablation group)			x						
ECG	x†				x	x	x		
48 h Holter∗									
TTE	x‡					x	x		
(LAvolume, LVEF)									
Questionnaires:	x						x	x	x
AFEQT									
EQ-5D-5L									
AF symptoms	x				x	x	x		
EHRA Score; patients’ diary									
Blood tests (creatinine, glomerular filtration rate, BNP, potassium, thyroidal-stimulating hormone, blood count incl. hemoglobin, GOT, GPT, GGT, INR)	x§					x	x		
ILR interrogation		x			x	x	x	x	x
TEE (only intervention group)			x						
Physical examination	x				x	x	x		
Adverse event reporting	x		x	x	x	x	x	x	x
Phone call								x	x

AAT, antiarrhythmic drug therapy; AF, atrial fibrillation; BNP, brain natriuretic protein; EHRA, European Heart Rhythm Association; EQ-5D-5L, EuroQol 5-dimension, 5-level; EQT, **A**trial **F**ibrillation **E**ffect on **Q**uali**t**y-of-life; ER, emergency room; GGT, gamma-glutamyl transferase; GOT, glutamic-oxaloacetic transaminase; GPT, glutamate-pyruvate transaminase; ILR, implantable loop recorder; incl, including; INR, international normalized ratio; LA, left atrial; LVEF, left ventricular ejection fraction; TEE, transesophageal echocardiography; TTE, transthoracic echocardiography.

∗ Holter-ECG is recommended, not mandatory.

† ECG performed within clinical routine prior to d 0 may be used.

‡ TTE performed within clinical routine prior to d 0 may be used.

§ Blood sample performed within clinical routine prior to d 0 may be used.

### Implantable loop recorder

All study participants will receive an ILR (Reveal LINQ, Medtronic, MN) within 21 days of the baseline visit, and no later than the date of therapy initiation (ie, the cryoballoon ablation procedure or the start of antiarrhythmic drug treatment).

Patients in the ablation arm undergo the implantation procedure during their hospital stay for AF ablation. Patients in the usual-care arm undergo the implantation procedure either during their hospital stay at baseline (for inpatients) or within 21 days from baseline (for outpatients). The implantation procedure will be performed according to device instructions, standard of care, and current guidelines.

AF burden (time spent in AF) is collected by the ILR. The ILR provides a daily measure of the time spent in AF. The ILR will be enrolled in the CareLink system (Medtronic) for central blinded remote monitoring (for research only).

A core lab with blinded investigators, assisting the ERC, will assess the detected AF episodes.

### Catheter ablation group

Patients randomized into the cryoballoon ablation group should receive the catheter ablation within 21 days. The decision to perform transesophageal echocardiography prior to ablation is made per the physician’s discretion, according to current guidelines. For the sake of comparability of data, the ablation should be performed with the Arctic Front Advance Cardiac Cryo Ablation Catheter System (Medtronic). If the cryoballoon ablation procedure should fail or be skipped for any reason, the patient will remain in the study and will be followed according to the intention-to treat principle. The ablation strategy of this study group has been described previously.^16^ Regarding the ablation strategy, PVI is the primary ablation target. Conduction of the cryoballoon ablation strategy can be performed at the discretion of the operator. In the case of ongoing AF after PVI, cardioversion is attempted. If cardioversion fails, further ablation may be performed at the discretion of the operator. In the case of concomitant typical atrial flutter, cavotricuspid isthmus ablation should be performed with radiofrequency current.

### Usual care group

Patients randomized into the usual care group should start or be maintained on antiarrhythmic drug therapy within 21 days, based on the decision of the investigator, according to current ESC guidelines.^1^ Usually, class Ic AAD (eg, flecainide, propafenone) will be used apart from patients with comorbidities and/or impaired left ventricular function, who will preferably receive amiodarone. If necessary, cardioversion can be performed to establish sinus rhythm according to current ESC guidelines.^1^ Oral anticoagulation and treatment of comorbidities will be performed at the discretion of the investigator, according to current guidelines, for both study arms.^1^

### Statistical methodology

The study’s statistical analysis plan outlines the following: The primary analysis is related to atrial tachyarrhythmias and AF. A survival table and a Kaplan-Meier plot with stratified survival curves by groups will be shown. A log-rank test will be applied to examine differences of the hazard function between the treatment groups. A *P*-value of < 0.05 will be considered significant.

Secondary analyses are associated with QoL, left ventricular ejection fraction, and brain natriuretic protein over time. (Generalized) linear mixed models will be used to examine differences between ablation groups. AF burden and the rehospitalization rate will be analyzed descriptively. The time to first rehospitalization will be presented as survival tables and plots. Secondary endpoints were considered exploratory.

Procedure-related complications, including the index and any repeat catheter ablation, ILR implantation, and cardioversion, will be observed. As the serious adverse events are captured in free text, they will be harmonized (by the trial steering committee) before analysis. Each single type of adverse event for a subject will be shown only once.

All serious adverse events, and their duration, resolution, cardiac cause, and severity are listed. The summary table comprises only the treatment-related adverse events with a cardiac cause.

The regular study phase concludes after 12 months, including site monitoring as well as ERC and data and safety monitoring board oversight. During the subsequent prolonged follow-up period (up to 24 and 36 months), rhythm-related endpoints via ILR, and serious adverse events, will continue to be collected.

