To date, no robust scientific evidence has been gathered from large-scale studies comparing early catheter ablation vs antiarrhythmic drug therapy in AF patients presenting to the ED with recent-onset AF, including those experiencing a first episode. Additionally, the impact of catheter ablation in patients with persistent AF has not been investigated in sufficient detail, as reflected by the current guideline recommendation.^1^

Given that the relevance of AF burden as a study endpoint has gained increasing clinical awareness, continuous follow-up via an implantable loop recorder is considered an essential component of current AF study designs.^19^^,^^20^

Therefore, the purpose of the From the Emergency Department, Directly to Ablation of Atrial Fibrillation (EMERGE Cryo) study is to evaluate the efficacy and safety of an early rhythm control treatment of recent-onset AF by catheter ablation with the cryoballoon vs usual care (AAD), with respect to arrhythmia recurrence, rehospitalization, and heart failure, in patients presenting to the ED or as an emergency visit in an outpatient clinic.

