### Secondary effectiveness endpoints of the EMERGE Cryo study are as follows:

•AF burden between 3-12 months after randomization; AF burden is defined as the percentage of time the study participant is in AF during the observation period;•AF burden between 0-3, 3-6, and 6-12 months after randomization;•freedom from AF (> 30 seconds) through 3-12 months of follow-up care;•freedom from atrial tachycardia and atrial flutter (> 30 seconds) through 3-12 months of follow-up care;•analysis of amount of symptomatic vs asymptomatic atrial tachyarrhythmia recurrences through 3-12 months of follow-up care (reported as number of recurrence episodes);•rehospitalization rate due to cardiovascular disease (AF, worsening of heart failure, cardiovascular disease);•progression of heart failure defined as trend in left ventricular ejection fraction and trend in brain natriuretic protein;•improvement of quality of life (QoL) at 12 months compared to baseline (**A**trial **F**ibrillation **E**ffect on **Q**uali**t**y-of-life [AFEQT] questionnaire and EuroQol 5-dimension, 5-level [EQ-5D-5L] questionnaire); and•safety / complications: device- and procedure-related adverse events, serious adverse events, and cardiovascular-related adverse events will be collected to determine and compare the safety profile of the 2 treatment groups.

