## Conclusion

The EMERGE Cryo study is an investigator-initiated, prospective, 2-arm, randomized, open-label, blinded endpoint, multi-centre study to investigate the impact of first-line ablation in patients presenting at the ED with recent-onset paroxysmal or persistent AF. The trial is currently ongoing and completion of patient enrollment is planned for fall of 2025. The trial's outcome aims to determine the value of early catheter ablation in AF patients presenting to the ED, irrespective of symptoms, and AF phenotype, and including those with recent-onset AF or their first clinical AF episode. As a result, this study has the potential to address evidence gaps, reduce the AF burden in patients, and lower rehospitalization rates throughout an extended follow-up period.

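### AF burden and rehospitalisation get only a descriptive analysis, so the trial plans no between-arm estimate or interval for two outcomes that its purpose and rationale rely on

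*Protocol article*

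**What the plan says.** The Statistical methodology section introduces its content as what the statistical analysis plan lays down. It then treats the secondary endpoints in two ways.

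- **Compared between arms:** quality of life, left ventricular ejection fraction and BNP are to be analysed over time with (generalized) linear mixed models aimed at group differences.
- **Described only:** "AF burden and the rehospitalization rate will be analyzed descriptively". For the event-time version, "The time to first rehospitalization will be presented as survival tables and plots". No test, effect measure or interval is named for either.

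One label covers both classes: "Secondary endpoints were considered exploratory".

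Elsewhere the article gives the two described outcomes more weight. The purpose at the end of the introduction is to evaluate efficacy and safety "with respect to arrhythmia recurrence, rehospitalization, and heart failure". The introduction justifies continuous loop-recorder follow-up by the growing relevance of AF burden as an endpoint. Burden heads the list of secondary endpoints and is defined there as a percentage of time in AF. The Implantable loop recorder section states that "The ILR provides a daily measure of the time spent in AF". The ILR part of the Discussion offers burden as a complement to the 30-second primary endpoint. The Conclusion says the study has the potential to "reduce the AF burden in patients, and lower rehospitalization rates throughout an extended follow-up period".

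**The concern.** The primary endpoint reduces each patient's continuous record to whether and when any atrial arrhythmia longer than 30 seconds occurred. Burden is the listed endpoint that measures how much AF remains, and it needs an implant in every patient. If it is only described by arm, the report will show two summaries side by side. Readers will compare them anyway, without an agreed contrast or a statement of uncertainty. The same holds for rehospitalisation, which is part of the trial's declared purpose.

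The choice is also uneven. An exploratory label does not explain it, because three equally exploratory outcomes do get comparative models. A contrast chosen after the data are seen would carry less weight than one fixed now.

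**Working it through.** **1. The plan's own figure.** The only sample-size figure is 350, for the primary endpoint. Inputs from the Sample size calculation section: 60% against 45% event-free at 12 months, two-sided alpha 0.05, 80% power, log-rank test, 10% dropout.
- Hazard ratio = ln(0.60)/ln(0.45) = 0.640.
- Events (Schoenfeld) = 4 × (1.960 + 0.842)² / (ln 0.640)² ≈ 157.3, so 158.
- With dropout treated as exponential censoring over 12 months (an assumption), the mean event probability is 0.453 and N ≈ 347 to 348, close to 350. Dividing by 0.9 instead gives 370.

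The figure is reproduced, but it says nothing about burden or rehospitalisation.

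**2. What the same patients could show on burden.** Evaluable patients: 350 × 0.9 = 315, or n = 157.5 per arm. Let P be the probability that a randomly chosen ablation patient has a lower 3–12-month burden than a randomly chosen usual-care patient, counting ties as one half.
- 95% half-width near P = 0.5, no ties: 1.96 × √[(2n + 1)/(12n²)] = 1.96 × √(316/297,675) = 0.064.
- Assume zero burden in 52.5% of patients, the mean of the planning rates 60% and 45%. The variance then shrinks by about 1 − 0.525³ = 0.855, giving 0.064 × √0.855 = 0.059.

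Burden can therefore be estimated to about ±0.06 on a scale where 0.5 means no difference.

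**3. What they could show on rehospitalisation.** The article gives no rate, so the 12-month proportion is an assumption. Half-width of the 95% interval for a difference between equal proportions p: 1.96 × √[2p(1 − p)/157.5]. The last column is the lower proportion detectable with 80% power.

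| Assumed proportion | Half-width | Detectable against |
|---|---|---|
| 10% | 6.6 points | 2.4% |
| 20% | 8.8 points | 8.9% |
| 30% | 10.1 points | 16.6% |
| 40% | 10.8 points | 25.2% |

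Only large differences (7.6 to 14.8 points) would be detectable. This agrees with the article's own caveat on power. An interval would show it, whereas two bare rates would not.

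**4. Statements set side by side.**

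| Outcome | Weight in the article | Planned comparison |
|---|---|---|
| QoL | secondary, exploratory | mixed model |
| LVEF, BNP | secondary, exploratory; heart failure is in the purpose | mixed model |
| AF burden | secondary, exploratory; reason for the recorder; in the Conclusion | none |
| Rehospitalisation | secondary, exploratory; in the purpose and the Conclusion | none; tables and plots |

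**The case against.** **Descriptive reporting is modest and consistent.** The Conclusion says only that the study has the potential to bring these benefits, secondary endpoints are exploratory, and the Discussion concedes that the trial is not powered for hospitalisation. This stands against any charge that the article announces burden or rehospitalisation findings; a reader might infer that, but the wording does not support it. It does not explain why equally exploratory outcomes are modelled. The power caveat covers hospitalisation and is not stated for burden, and low power is a reason to show an interval.

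**The detail may be in the unseen analysis plan.** A descriptive analysis may include arm-wise intervals, and the article is a condensation. But it attributes the descriptive choice to that plan, so this is a stated choice and not an omission.

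**A reader might infer that a highly powered burden test is being thrown away.** With zero-burden shares of 60% and 45% and log-normal burden (SD 2, an assumption) in the rest, simulation gives a rank test about 71% power when burden among patients with recurrence is equal, and 90% and 98% when it is halved or quartered. Most of this comes from the 60%/45% split, which the primary log-rank test already uses. With no burden difference among those patients, P is already 0.60 × 0.45 × 0.5 + 0.60 × 0.55 + 0.40 × 0.55 × 0.5 = 0.575. With 52.5% at zero in both arms, power falls to about 11% (halved) and 27% (quartered). Across SD 1 to 3 the ranges are about 30% to 7% and 71% to 17%. So the gain beyond the primary analysis may be small.

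**A reader might also blame the episode count.** Symptomatic and asymptomatic recurrences are "reported as number of recurrence episodes", and a count treats months of continuous AF as one episode. That is a separate endpoint with no test named in the article. Burden is a percentage of time, and rehospitalisation is a rate and a time to first event, so the count affects neither.

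**Conclusion.** The point holds as a cheap improvement. For two outcomes on which the purpose, the monitoring rationale and the Conclusion lean, the stated plan yields no between-arm estimate or interval, while comparable exploratory outcomes receive one. The purpose and the hedged Conclusion therefore go further than the planned analysis.

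A reader might conclude that the trial cannot inform these questions at all. That is too strong. The limit lies in the analysis and not in the data: allocation is randomised and burden is recorded daily. What is forgone is an interval of about ±0.06 on the probability of lower burden and of about ±7 to ±11 points on a 12-month rehospitalisation difference. These figures assume 315 evaluable patients, about half of them at zero burden, and rehospitalisation proportions of 10% to 40% that the article does not give. The primary analysis is unaffected.

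**What to change.** Replace the descriptive analysis with prespecified exploratory between-arm estimates, each with a 95% confidence interval.

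- **AF burden, months 3–12:** a rank-based comparison stratified by AF type (paroxysmal or persistent), reported as the probability of lower burden with ties at zero counted as one half. A median shift is a poor choice here, because with about half the patients at zero it may be close to zero whatever happens in the rest.
- **Cardiovascular rehospitalisation:** a rate ratio from a count model with log follow-up time as offset, and a hazard ratio for first event beside the planned survival plots. Do not count the protocol-required ablation and recorder-implantation stays. The Implantable loop recorder section places implantation within the ablation admission in one arm, and within the baseline stay or up to 21 days later in the other, so counting these stays would build in a difference between arms.

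Keep the exploratory label and the caveat on power for hospitalisation. If the authors prefer to stay descriptive, the alternative is to narrow the purpose and the Conclusion to match.

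The cost is analysis-plan wording and a little code, with no new data. The article reports 319 of 350 patients enrolled and the trial ongoing, so the change can precede complete outcome data. The small downside is a few more exploratory comparisons without multiplicity adjustment, which the report should state.

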## Methods

### Study design

The EMERGE Cryo study is an investigator-initiated, prospective, 2-arm, randomized, open-label, blinded endpoint, multicentre study to investigate the impact of first-line ablation in patients presenting to the ED or as an emergency visit in an outpatient clinic with recent-onset paroxysmal or persistent AF, including patients with a first episode of AF. According to the statistical analysis plan, n = 350 patients will be enrolled at up to 13 German centres. Each site will contribute < 50% of subjects.

This study has been approved by regional ethics committees and is conducted in accordance with the Declaration of Helsinki and the International Council for Harmonisation Good Clinical Practice guidelines. Written informed consent was obtained from all patients. The trial is registered on ClinicalTrials.gov (NCT05294445).

The principal investigator (PI), and Asklepios Proresearch Institute was responsible for the development of the study protocol. The trial is supported by a steering committee. An independent data and safety monitoring board guides the trial. All serious adverse events and study endpoints are assessed by a blinded core lab and adjudicated by an independent endpoint review committee (ERC), which will be blinded to the randomization group.

The contract research organization RQM+ provides support with regard to monitoring of patient data, site supervision, site initiation, and closeout visits. The contract research organization and the study sites use secuTrial (interActive Systems GmbH, Berlin, Germany) as the electronic case-report form system.

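### The safety summary table is restricted to treatment-related events of cardiac cause, which is narrower than the safety endpoint the trial sets out to compare between arms

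*Protocol article*

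**What the plan says.** The list of secondary endpoints closes with safety. It states that "device- and procedure-related adverse events, serious adverse events, and cardiovascular-related adverse events will be collected" and gives the purpose as "to determine and compare the safety profile of the 2 treatment groups". The introduction also names safety, next to efficacy, as part of what the trial is meant to evaluate.

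Statistical methodology, which attributes its content to the trial's SAP, deals with safety in three statements:

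- On procedures: "Procedure-related complications, including the index and any repeat catheter ablation, ILR implantation, and cardioversion, will be observed".
- On serious events: "All serious adverse events, and their duration, resolution, cardiac cause, and severity are listed".
- On tabulation: "The summary table comprises only the treatment-related adverse events with a cardiac cause".

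It also says that a given type of event is shown once per patient, and that secondary endpoints are exploratory.

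**The concern.** The endpoint and its analysis have different scopes. The endpoint covers serious events of any cause and procedural or device events in any organ system. The table admits an event only if it is judged related to treatment and also cardiac in cause.

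The trial compares an invasive procedure with drug treatment, in a population that includes asymptomatic patients and patients in a first episode. Readers will weigh benefit against total harm in each arm. If the one table described omits part of that harm, the published comparison will be narrower than the endpoint promised, and the omitted events will have to be counted by hand from a listing. The word only in the tabulation statement makes this an explicit restriction, not a detail left open by a condensed article.

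**Working it through.** The plan states no safety figure, so there is nothing to reproduce. The check sets the endpoint definition against the three analysis statements.

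| Kind of event | In the endpoint? | Where Statistical methodology puts it | In the summary table? |
|---|---|---|---|
| Treatment-related, cardiac cause, and in an endpoint class | Yes | Table; also the listing if serious | Yes |
| Procedure- or device-related, non-cardiac, serious | Yes | Listing; observed if a procedural complication | No |
| Procedure- or device-related, non-cardiac, not serious | Yes | Observed if a procedural complication; otherwise no stated place | No |
| Serious drug toxicity, non-cardiac | Yes, as a serious event | Listing | No |
| Serious event judged unrelated to treatment | Yes | Listing | No |
| Non-serious cardiovascular event judged unrelated, or without a cardiac cause | Yes | No stated place, unless a procedural complication | No |
| Non-serious, non-cardiovascular drug effect | No | Outside the endpoint | Not applicable |

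Five of the six kinds of event that belong to the endpoint are outside the table. For those five, the text offers a line listing, observation, or nothing, and it states a comparison by arm for none of them.

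**Illustration of size (assumed rates).** The documents give no complication rates and no split by cause. The only trial figures used are 350 patients and 1:1 allocation.

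- Patients per arm: 350 / 2 = 175.
- Assume 5% have a treatment-related serious event: 175 × 0.05 = 8.75, about 9 patients.
- Assume 30% to 60% of these are non-cardiac, so the table keeps 70% to 40%.
- Upper end: 8.75 × 0.70 = 6.1 patients, and 6.1 / 175 = 3.5%.
- Lower end: 8.75 × 0.40 = 3.5 patients, and 3.5 / 175 = 2.0%.

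Under these assumptions a 5% rate is displayed as 2.0% to 3.5%. This covers the cardiac filter only. The relatedness filter would remove further serious events, by an amount the documents do not allow one to estimate.

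**The case against.** The best defence is that nothing is hidden. Every serious event is listed whatever its cause, with cardiac cause as one attribute. Procedural complications have their own sentence with no cardiac filter, so an access-site bleed or a nerve injury after ablation would be captured there. Harmonising terms before analysis and showing each type once per patient suggest that events will be grouped, not just listed. The article condenses a SAP that is not shown, and it does not say that this is the only safety table. Safety is exploratory, a data and safety monitoring board oversees the trial, and the gap can be closed at reporting.

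Most of this is fair and limits the severity. It does not remove the mismatch. A listing is not a comparison, observing complications is not an analysis, and the one table that is described carries an explicit restriction that the endpoint lacks.

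Three stronger readings are tempting, and the documents do not support them:

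- **That steering-committee coding contradicts blinded adjudication.** The steering committee handles free-text serious events: "they will be harmonized (by the trial steering committee) before analysis". Study design has serious events "adjudicated by an independent endpoint review committee (ERC), which will be blinded to the randomization group". Harmonising terms and adjudicating events are different steps, and both can be done as described.
- **That drug reactions are wrongly left unnamed.** The sentence naming ablation, loop-recorder implantation and cardioversion is about procedures, so drug reactions would not be expected in it. Non-serious, non-cardiovascular drug effects are not in the endpoint, so the table cannot drop them from the promised comparison. Scheduled thyroid and liver tests do not change that. Serious drug toxicity is affected, because it counts as a serious event.
- **That the filter could reverse the direction of the safety difference.** This would need event rates and non-cardiac shares by arm. The documents give none, so it is no more than an arithmetical possibility.

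**Conclusion.** The point holds as a mismatch of scope between the safety endpoint and its tabulation. Followed as written, the plan gives a summary narrower than the comparison it promises, leaving out non-cardiac procedural and device events, non-cardiac serious events and events judged unrelated. Severity is moderate: the endpoint is secondary and exploratory, the primary analysis is unaffected, and no serious event is lost from the report.

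The conclusion rests on the wording alone and assumes that the article reports the SAP's restriction faithfully. If the SAP also tabulates each endpoint class by arm, the defect shrinks to a misleading sentence in the article. The numerical illustration depends wholly on assumed rates and is not evidence of the size of the effect.

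**What to change.** Replace the tabulation sentence in Statistical methodology with wording such as:

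> For each of (a) all serious adverse events, (b) all adverse events related to a device or procedure, in any organ system, and (c) all cardiovascular adverse events, the number of patients with at least one event and the number of events will be summarised by randomised arm. Each summary will be broken down by cardiac or non-cardiac cause and by relatedness to treatment.

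The present table can stay as a subset of these. The rule of showing each event type once per patient should be stated to govern the patient counts only, so that it does not suppress the event counts.

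The endpoint already calls for these events to be collected, so the change needs no new data and does not affect the sample size. The cost is one or two longer tables and higher displayed event rates. In mid-August 2025, 319 of 350 patients were enrolled, so 12-month follow-up of the last patients was still ahead. The wording should be settled and dated before safety data are compared by arm.
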